### Outcomes {12}

#### Primary outcome: quality-of-care measures

The primary outcome of this trial is provider quality of care. Provider quality of care in both arms is measured via retrospective chart abstraction at baseline and again for each respective patient participant. Care provided over a 6-month timeframe is evaluated for adherence with 13 primary care UI QIs we previously developed, to allow adequate time to comply with the QIs [8] (Table 1). For each chart abstraction, a given eligible indicator is scored as a dichotomous measure (met vs. not met). Aggregate scores are measured as proportions: encounters where patients receive the recommended care vs. total encounters where patients are eligible for specific QIs. The results will be reported as percentages ranging from 0 to 100%.

#### Secondary provider outcomes

Data on referral rates are also collected at the 6-month chart abstraction to assess overall specialty referral rates and the presence of an appropriate delay of referrals, in which referrals are placed only after first-line treatment is initiated.

At baseline, providers complete a demographic questionnaire and a modified version of the Pelvic Floor Awareness and Knowledge Survey (Fig. 3). The PFAKS is a 31-item validated questionnaire assessing knowledge of three pelvic floor disorders: pelvic organ prolapse (11 items), stress urinary incontinence (SUI) (10 items), and overactive bladder (OAB) (10 items) with questions on condition pathophysiology, management, and quality of life for these conditions [17]. The modified PFAKS excludes the 11 pelvic organ prolapse items.

**Fig. 3 Fig3:**
[figure not shown]
SPIRIT diagram of patient participant timeline (same for both arms). Legend: Allocation omitted, as randomization occurs at office level and patients are recruited from PCP upcoming visit

#### Patient reported outcomes

At baseline, all patient participants complete demographic questionnaires (Fig. 3). Symptom severity and disease-specific quality of life (QoL) are assessed with the Urinary Distress Inventory (UDI-6), Incontinence Impact Questionnaire, Short Form (IIQ-7), and the International Consultation on Incontinence Questionnaire-Urinary Incontinence Short Form (ICIQ-SF) [20, 21]. The UDI-6 (6-item, 5-point Likert scale) and IIQ-7 (7-item, 4-point Likert scale) are validated questionnaires measuring UI impact on QoL with a range of 0 to 100. The ICIQ-SF (6-item, 5-point Likert scale) is a validated questionnaire assessing symptom severity and QoL with a range of 0 to 21.

Patients also complete the following: the Patient Global Impression of Improvement (PGI-I), a single-item measure for symptom response to therapy [22]; the 9-Item Shared Decision Making Questionnaire (SDM-Q-9), assessing patient-perceived involvement in the clinical decision-making process via both Likert scale (range of 0 to 100) and free-response sections [23]; and lastly, the same modified PFAKS given to providers. A summary of the patient assessment timeline is shown in Fig. 3.

Spanish translations for all surveys are available for Spanish-speaking patients. The ICIQ-SF, UDI-6, and SDM-Q-9 have been validated in Spanish [24–26]. The PGI-I and modified PFAKS questionnaires have been translated into Spanish by certified translators, and the Spanish translation of the PFAKS is currently undergoing validation.

### Participant timeline {13}

Intervention PCPs receive the academic detailing portion of the intervention prior to patient recruitment. Six-month PFAKS is timed based on their office’s UI lecture (Fig. 3). Patient recruitment opens for intervention PCPs once their individual coaching session (i.e., lecture followed by a review of prior care with a clinical champion) is completed and is closed once 10–13 patients per provider are enrolled; the exact timeline will differ between PCPs based on factors such as their patient population (e.g., proportion eligible) and number of outpatient visits per week. Since routine care PCPs do not receive academic detailing, 6-month PFAKS will be timed based on the enrollment date. Patient recruitment in this arm begins once enrolled PCPs complete the baseline surveys. Both patients and PCPs in the routine care arm complete an identical battery of surveys as those in the intervention arm.

Patient participants are enrolled 1–2 weeks prior to an upcoming appointment with their PCP and complete the baseline survey battery upon enrollment. Patient participation includes the completion of baseline, 3-, and 6-month surveys; a patient is considered finished with the study once they complete the 6-month surveys (Fig. 3).

### Sample size {14}

All power estimates were performed assuming mixed-model regression modeling to account for the nested study design (patients within providers within offices) using PASS 2020 software [27]. As randomization will occur at the office level, power was computed assuming an average of 3 providers per office with an intra-cluster correlation of 0.04 (consistent with previous reports for process-of-care outcomes [28]) and a correlation of 0.16 across patients within each provider. Preliminary data found the average baseline quality of care to be 40% with a standard deviation of 20% [8, 18]. Therefore, to detect a change of 6% in total scores at an alpha level of 0.05 with 80% power, the study will require at least 720 patients from 48 offices (360 patients from 24 offices per study arm; see Fig. 1).

We conservatively estimate this sample size can detect a minimum odds ratio of 0.52, which is equivalent to a decrease in referral rates from 60 to 44% between the two treatment arms of the study, with 80% power at the 0.05 significance level. For patient-reported outcomes, our preliminary data had an average score of (± SD) of 35 (± 20) for the UDI-6 and 18 (± 20) for the IIQ-7. The study is powered to identify a difference of 6 points or greater in each of the two measures between study arms.

### Recruitment {15}

Prior to PCP recruitment, the study team met with health system and primary care leadership at each participating site to identify and select eligible primary care offices, with permission from health system, primary care, and practice leadership. Eligible PCPs that wished to participate were then recruited by the study team during individual office meetings.

For patient recruitment, a data analyst generates a weekly list of adult women with upcoming appointments in the next 10–14 days. One week before the scheduled appointments, the research team emails eligible patients the screening survey. Patients who answer that they (1) have new or worsening bothersome UI that they would like to address with their PCP and (2) have not been seen by a urologist or urogynecologist for UI in the past 2 years are then presented with the consent form from the same screening survey.

Because this is a pragmatic trial, variation in screening is allowed based on the population served. For example, to improve recruitment from a safety-net hospital with a large Spanish-speaking patient population with varying internet access, participants from this health system are recruited via a telephone-based screening performed by a fluent Spanish-speaking research team member.

## Assignment of interventions: allocation

### Sequence generation {16a}

Offices were assigned to study arms using randomization lists generated using Wei’s Urn method (to allow for equal sample sizes). Randomization at the practice level was done for all four sites by the study biostatistician 1:1 to each study arm, stratified by study site and office specialty (family medicine, gynecology, geriatrics, and general internal medicine), using PASS 2020 software [27]. Physicians working within a given practice received the same designation to prevent cross-contamination of intervention materials.

### Concealment and implementation {16b} {16c} {17a} {17b}

Office-level allocation was recorded on site-specific Real Electronic Data Capture (REDCap) servers (a password-protected data management platform). Individual PCPs were not randomized independently. Rather, once an office was assigned to a study arm, all PCPs recruited from that office inherited the office-level allocation. Office-level allocation was concealed from PCPs during recruitment.

Recruitment of PCPs from allocated offices was conducted by site-specific clinical champions, with assistance from trained research coordinators using standardized recruitment scripts that did not reference intervention assignment, thereby preventing inadvertent disclosure. PCPs were informed prior to enrollment that randomization occurred at the office level; however, they were not informed of their specific office’s assignment until after enrollment was complete. Though not provided as part of the enrollment process, patients can be informed of their PCP’s allocation provided upon request post-enrollment.

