**Fig. 2 Fig2:**
[figure not shown]
SPIRIT diagram of practice and PCP timeline. Legend: Allocation occurs at practice-level prior to PCP enrollment. Timepoint (*t*) at which PCP’s final patient participant is enrolled differs based on individual provider

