#### Academic detailing

Enrolled PCPs receive academic detailing prior to patient recruitment. This portion of the intervention integrates principles of Educational Outreach, utilizing stepwise application of evidence-based techniques (i.e., baseline knowledge inventories, targeted interventions, etc.) to improve clinical decision-making [16]. First, PCPs complete their baseline UI knowledge assessment via the Pelvic Floor Awareness and Knowledge Survey (PFAKS), a 31-item validated pelvic floor disorder knowledge questionnaire [17]. Once complete, the study team holds an in-person or virtual lecture at intervention practices. Providers unable to attend receive a one-on-one lecture via Zoom. Lectures are led by a UI clinical champion, either a urologist/urogynecologist or PCP from that site who is part of the research team and has expertise in UI management. The lecture centers on a set of thirteen previously developed and tested quality-of-care indicators (QIs) that cover all aspects of non-surgical management of UI, including history and physical examinations (i.e., pelvic exam), urinalysis, initiation of conservative treatment (i.e., lifestyle/behavioral interventions, pelvic floor training, medication, and when to refer to a UI specialist in urogynecology (Table 1)). The QIs were independently developed using the RAND Appropriateness, or Delphi, Method [13] and are validated for use in a diverse population [8, 18, 19]. PCPs also receive a pocket guide with a treatment algorithm.

Within a month after the lecture, UI specialists provide individualized coaching for intervention PCPs. This includes a one-on-one review of the PCP’s baseline quality of care for UI, as measured by retrospective chart abstraction of up to 5 previous UI encounters. Baseline charts are identified by a diagnosis code for UI (Appendix A). After reviewing prior care, the UI specialist offers individualized recommendations. Intervention PCPs are then ready for patient recruitment. Baseline chart abstraction is also performed in the routine care cohort, although without the individualized coaching sessions.

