### Confidentiality {27}

All patient and PCP data is housed on site-specific REDCap servers only accessible to respective site’s study team through role-based permissions. To protect confidentiality, patient and provider data are deidentified at the time of entry and labeled only with a REDCap-generated unique study identifier. No direct personal identifiers (e.g., name, medical record number, date of birth) are stored in the analytic dataset.

Linkage between the study identifier and identifiable information, when required for study operations (e.g., recruitment tracking or follow-up), is maintained locally at each site in a secure, access-restricted file and is not shared across sites. Any data shared between sites is deidentified.

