Hispanic women experience higher rates of stress and mixed UI compared to their non-Hispanic counterparts [41], yet often receive suboptimal care compared to other ethnic groups. Past analysis of Medicare data (1999–2001) also revealed disparities in that Caucasian and Hispanic women with a diagnosis of stress UI were more likely to undergo sling surgery than black or Asian women. Furthermore, Spanish-speaking patients tend to have less understanding of their condition and greater anxieties and resistance regarding treatment options offered compared to their English-speaking counterparts [42]. As such, the study team placed significant care during the design and implementation of the study to ensure substantial recruitment from this patient population. This includes the addition of phone-based screening with Spanish-speaking research team members and formulation and validation of Spanish versions for all questionnaires. However, despite these efforts, potential limitations remain when assessing such process-of-care outcomes due to structural and cultural factors outside the realm of individual providers.

As a multi-institution pragmatic study, there are potential limitations to the study’s execution, such as the lack of blinding of PCPs, patient participants, and study staff. However, we have reasons to believe this design feature will not significantly bias the results: office-level randomization limits avenues for cross-contamination of educational material and CDS tools, and providers in routine care offices have the opportunity to receive a delayed intervention. Although chart abstractors cannot be blinded given the makeup of the EHRs, their methods of QI assessment are strictly standardized, with detailed scoring rubrics and protocols developed to limit the potential bias and ensure inter-rater reliability.

Our assessment of incontinence outcomes is purposefully broad and encompassing, as we aim to measure and combine outcomes of different non-surgical treatments for stress and urge UI. We have excluded objective outcome measures, such as voiding diaries or pad tests, as we seek to minimize the burden to patients and providers. However, our study is nonetheless powered to detect a clinically meaningful difference in outcomes pertinent to patients between intervention and routine care groups, despite variation in treatment, case mix, and patient demographics.

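### PCPs were recruited after their office was allocated, by champions whose role also delivers the intervention; concealment is stated only towards PCPs, so approach or effort that differs by arm is not excluded

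*Protocol article*

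**What the plan says.** The order of events is clear. The Fig. 2 legend says "Allocation occurs at practice-level prior to PCP enrollment", and Concealment and implementation says "once an office was assigned to a study arm, all PCPs recruited from that office inherited the office-level allocation". The same section names the recruiters: "Recruitment of PCPs from allocated offices was conducted by site-specific clinical champions, with assistance from trained research coordinators".

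The only party from whom the arm is said to be hidden is the PCP: "Office-level allocation was concealed from PCPs during recruitment". The supporting measure is "standardized recruitment scripts that did not reference intervention assignment, thereby preventing inadvertent disclosure". PCPs learned their arm once enrolment was complete. The Recruitment section adds that PCPs who wished to take part were recruited at individual office meetings.

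On the champions' other duties, Academic detailing says "Lectures are led by a UI clinical champion, either a urologist/urogynecologist or PCP from that site who is part of the research team", and Participant timeline gives a clinical champion the review of prior care as well. The allocation is recorded on site-specific REDCap servers. The Confidentiality section describes patient and PCP data as "housed on site-specific REDCap servers only accessible to respective site’s study team through role-based permissions". The Discussion lists as a limitation "the lack of blinding of PCPs, patient participants, and study staff".

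**The concern.** Randomising offices balances the offices. It does not balance providers who are chosen from those offices after the arm is fixed. With about three PCPs per office (72 PCPs in 24 offices per arm), the enrolled PCPs are volunteers and may be only some of those eligible. Who ends up in the trial depends partly on whom the recruiter approaches and how hard the recruiter tries.

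A champion who knew the arm could, without intending it, look for more engaged PCPs at offices where the champion will later lecture and coach. The arms would then differ in provider quality before any intervention, and provider quality of care is the primary outcome. A script controls what the PCP hears. It does not control whom the recruiter approaches or how persistently.

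The Discussion gives three reasons for expecting little bias from the lack of blinding: limited contamination, a delayed intervention for routine-care offices, and standardised chart scoring. None of them bears on which providers were recruited.

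**Working it through.** **1. What the text covers.**

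| Question | Answer in the article |
|---|---|
| Is the office allocated before PCPs enrol? | Yes (Fig. 2 legend; Concealment and implementation) |
| Do the recruiters share a role with those who deliver the intervention? | Yes, clinical champion (Academic detailing; Participant timeline) |
| Is the arm hidden from PCPs while they decide? | Yes |
| Is the arm hidden from recruiters? | Not stated; study staff are described as unblinded |
| Was every eligible PCP approached? | Not stated; those who wished to take part were recruited at office meetings |
| Was the office's PCP list closed before its arm was released? | Not stated |

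**2. Reproduce the plan's sample size, to fix the variance structure.** Inputs from the Sample size section: difference 6 points, SD 20, alpha 0.05 (taken as two-sided), power 80%, 3 providers per office, office correlation 0.04, within-provider correlation 0.16. With 15 patients per office (Abstract), that is 15/3 = 5 patients per provider.

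- Without clustering: 2 × (20 × (1.960 + 0.842)/6)² = 174.4 per arm.
- Design effect: 1 + (5 − 1) × 0.16 + 5 × (3 − 1) × 0.04 = 2.04.
- 174.4 × 2.04 = 355.8 per arm, which needs 24 offices of 15, so 360 per arm and 720 in total. This matches the plan; power at 360 per arm is 80.5%.

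In this formula 0.16 is the whole correlation between two patients of one provider, including the 0.04 shared through the office. Treating the two as additive (0.20 within provider) gives 780, not 720.

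**3. Standard error of the arm difference.** 20 × √(2 × 2.04/360) = 2.13 points.

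**4. The spread on which selection can act.** Choosing PCPs inside an already allocated office can use only the differences between PCPs within that office: √(0.16 − 0.04) × 20 = 6.9 points.

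**5. Illustration.** Assume no true effect and a shift between arms in the mean quality of recruited PCPs, in units of that SD. The rejection probability is 1 − Φ(1.96 − b/SE) + Φ(−1.96 − b/SE), where b is the bias.

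| Assumed shift (SD) | Bias b (points) | Share of the 6-point target | False-positive rate |
|---|---|---|---|
| 0 | 0 | 0% | 5% |
| 0.1 | 0.7 | 12% | about 6% |
| 0.25 | 1.7 | 29% | about 13% |
| 0.5 | 3.5 | 58% | about 37% |

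The shifts are assumptions. The article gives nothing from which to estimate the true one, which may be zero.

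**The case against.** The strongest reply is that the usual route for this bias is blocked. PCPs volunteered at office meetings without knowing their arm, so acceptance could not depend on it, and recruiters worked from a standard script. What remains is uneven effort by a recruiter, which the article nowhere describes. Baseline quality of care is abstracted in both arms and PCPs complete the Pelvic Floor Awareness and Knowledge Survey (PFAKS) at baseline, so an imbalance would be visible. A condensed article may also leave REDCap permissions to the full protocol.

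Much of this stands. Masking the PCPs is a real protection, and meetings and scripts narrow the gap. They do not close it, because the article does not say that everyone eligible was approached or that recruiters were masked. Seeing an imbalance at baseline is also different from preventing it or adjusting for it.

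Three stronger readings are tempting and are not supported:

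- *Recruiters knew the arm and chose PCPs accordingly.* No section says so. Knowledge of the arm is an inference from unblinded staff, site-held allocation and the champions' duties. The Discussion's remark on blinding is general, and the Confidentiality sentence concerns patient and PCP data under role-based permissions.
- *Colleagues joined after their office's lecture and so knew the arm.* The article does not describe this. It only leaves open whether complete enrolment means the individual PCP's or the whole office's.
- *A provider SD of √0.16 × 20 = 8 points, with false-positive rates of about 7%, 16% and 47%.* That SD includes variation between offices, on which choice within an office cannot act.

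**Conclusion.** The point holds as a gap in the stated safeguards, not as evidence that selection took place. Offices were allocated before PCPs were recruited, the recruiters hold a role that delivers the intervention, and concealment is claimed only towards PCPs. The Discussion's reassurance does not reach provider selection. The statement that scripts prevent disclosure to PCPs can stand, but it should not be read as concealment from recruiters.

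The size is unknown. The illustrated range, 0.7 to 3.5 points of bias with false-positive rates of about 6% to 37%, rests on assumed shifts, a two-sided 5% test, the design effect that reproduces 720, and an analysis not adjusted for baseline quality. A small shift would do little harm, while a shift of half an SD would account for more than half of the target difference. The matter deserves action because any such bias falls directly on the primary outcome and most of the remedy uses data that the trial already collects.

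**What to change.** PCP recruitment is reported in the past tense and patient recruitment is under way, so most of the remedy lies in reporting and analysis.

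**For PCPs already enrolled**
1. State in Concealment and implementation who knew each office's allocation while PCPs were being recruited, and whether all eligible PCPs in an office were approached. If recruiters were masked and everyone was approached, saying so largely settles the point.
2. Tabulate enrolled PCPs' baseline QI score and PFAKS by arm. Add counts of eligible and approached PCPs where sites logged them; the article does not say that they did.
3. Adjust the primary mixed model for the PCP's baseline QI score, which is abstracted in both arms. The adjustment will be partial, since it rests on up to five earlier encounters per PCP.
4. Add a sensitivity analysis limited to PCPs enrolled before their office's arm was released or its lecture held. Routine-care offices have no lecture, so the release date, where recorded, is the cut-off that treats both arms alike.

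**For any PCP still to be enrolled**
5. Restrict the REDCap allocation field from whoever approaches PCPs, and close the office's PCP list before its arm is released.

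**Cost.** Some wording, one table, one covariate, one sensitivity analysis and, if enrolment continues, a permission setting. PCPs who join an office after its list is closed cannot be added, and the sensitivity analysis will contain fewer PCPs.

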## Data collection and management

### Data collection {18a}

Trained research staff conduct the chart abstractions considering all of the patient’s records when assessing whether the patient is eligible for and receives the indicated care [29]. Individual site PIs review QIs that require a detailed clinical assessment. Baseline and 6-month chart abstraction data are collected and stored via REDCap eCRF. Patient and PCP self-report data are collected via REDCap survey.

